### Criteria for discontinuing or modifying allocated interventions {11b}

Patients may prematurely drop out of the study under the following conditions:The personal wish of the patientThe occurrence or discovery of events or criteria after enrolment that contradict intervention

A premature end of the study or termination of the entire study may be considered under the following circumstances:New findings during the clinical trial that could endanger the safety of the participants (positive benefit-risk assessment no longer given)

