### Relevant concomitant care permitted or prohibited during the trial {11d}

Apart from the intervention and the close monitoring for POD during the postoperative visits, the participation in the study will not further affect the care of patients. Concerning the perioperative care, the anesthetic management protocols will not be modified by the trial. Induction and maintenance of anesthesia will be conducted according to the standard operating procedure of the clinic. The treating anesthesiologist will have access to the routinely used neuromonitoring devices and the indices of depth of anesthesia. If patients develop a POD, the treatment of productive delirious symptoms with antipsychotic drugs will be administered as prescribed by the treating ward physician.

At the Greifswald University Hospital, a delirium prevention unit has been implemented in the routine care of hospitalized patients of four departments (general surgery, orthopedy, internal medicine, and neurology). All patients over 65 years of age are screened daily by the unit, and non-pharmacological delirium prevention interventions are undertaken. Patients who are enrolled in the trial and admitted to one of these departments will not be visited or accompanied by the delirium prevention unit.

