### Outcomes {12}

#### Primary outcome measure

Incidence of POD as defined by having at least one positive 3D-CAM within the 10 visits in the 5 postoperative in-hospital days.

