## Statistical methods

### Statistical methods for primary and secondary outcomes {20a}

The statistical analysis will be based on the intention-to-treat principle, including all randomized patients in the groups to which they were assigned, regardless of the treatment received. The Statistical Analysis Plan will be publicly accessible on the clinical trial registry at https://drks.de/search/de/trial/DRKS00033703.

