### Methods in analysis to handle protocol non-adherence and any statistical methods to handle missing data {20c}

To address missing data, we will employ a two-pronged approach. For missing values assumed to be Missing Completely at Random (MCAR) or Missing at Random (MAR), we will utilize Multiple Imputation by Chained Equations (MICE). This method iteratively imputes missing values based on the relationships between variables, resulting in 30 complete datasets for subsequent analyses. In cases where the reason for missingness is known (informed missingness), targeted single imputation techniques will be employed. The specific imputation strategy (worst-case or best-case scenario) will be chosen based on the nature of the missing data. This approach mitigates the effects of dropouts or deviations from the protocol.

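### The discontinuation rule treats not giving or stopping stimulation as a reason to leave the study, which conflicts with the intention-to-treat analysis and can replace observable POD outcomes with imputed ones

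*Protocol article*

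**What the plan says.** Section {11b} of the Protocol article is headed as criteria for discontinuing or modifying the allocated intervention. The only consequence it gives for an individual patient concerns the study: "Patients may prematurely drop out of the study under the following conditions". Two conditions follow, the patient's own wish and the "occurrence or discovery of events or criteria after enrolment that contradict intervention".

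Section {20a} sets an intention-to-treat analysis, "including all randomized patients in the groups to which they were assigned, regardless of the treatment received". The primary outcome is "at least one positive 3D-CAM within the 10 visits in the 5 postoperative in-hospital days".

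Section {20c} covers missing data in two ways. Values assumed missing completely at random or at random get multiple imputation by chained equations with 30 datasets. For the rest: "In cases where the reason for missingness is known (informed missingness), targeted single imputation techniques will be employed". Worst or best case is to be chosen according to the nature of the missing data. The section concludes: "This approach mitigates the effects of dropouts or deviations from the protocol".

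On timing, enrolment is at least one day before surgery {11a}, allocation follows the order of enrolment within stratum {16b}, and the single stimulation session takes place afterwards in the PACU {11a}. The sample size section {14} requires 60 per group and includes 225 in total, allowing for about 20% dropout.

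**The concern.** An intention-to-treat analysis regardless of treatment received needs outcomes from patients who were not stimulated or whose session was cut short. Section {11b} allows exactly those patients to leave the study. The ten 3D-CAM visits take place in hospital and are already planned for every participant, so these outcomes would often be obtainable. If the visits end, the primary result rests on imputed values for these patients.

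Imputation is a weak substitute here for two reasons. First, if patients in the tACS arm who were not stimulated all leave, nobody in that arm shows what happens without stimulation. Multiple imputation by arm would then fill their outcomes from stimulated patients, which is not the effect regardless of treatment received. Second, the reason for this kind of exit is known, so the single-imputation branch would seem to apply, and its direction is not fixed.

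**Working it through.** **Inputs.** From section {14}: POD 19.7% and 4.9%, one-sided alpha 0.05, power 80%, chi-square test, 60 per group, about 20% dropout, total 225. The calculations use that chi-square test without continuity correction as an approximation to the planned logistic regression.

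**1. The plan's own figure.** With mean rate p̄ = (0.197 + 0.049)/2 = 0.123:

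n = [1.645·√(2·0.123·0.877) + 0.842·√(0.197·0.803 + 0.049·0.951)]² / (0.148)² = 59.8, so 60 per group. The odds ratio is 4.761. Total: 3 × 60 / 0.8 = 225, or 75 per arm. The plan's figures reproduce exactly. They allow for 75 − 60 = 15 patients per arm without an observed outcome.

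**2. Does the open imputation choice matter?** Take 12/60 sham and 3/60 tACS (20% and 5%, the whole-number counts nearest the planned rates) and 15 missing per arm. Use z = (p₁ − p₂)/√[p̄(1 − p̄)(1/n₁ + 1/n₂)].

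| Handling of the 15 missing per arm | Sham | tACS | z | One-sided p |
|---|---|---|---|---|
| Left out | 12/60 | 3/60 | 2.48 | 0.006 |
| All set to no POD | 12/75 | 3/75 | 2.45 | 0.007 |
| All set to POD | 27/75 | 18/75 | 1.60 | 0.054 |

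The same observed data fall on either side of 0.05 depending on that choice. Assigning the whole 20% allowance to this route is an upper bound, because the documents do not break dropout down by cause.

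Expected power with single imputation at the planned rates, 75 per arm:

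| Missing per arm | All set to POD | All set to no POD |
|---|---|---|
| 4 | 0.74 | 0.85 |
| 8 | 0.63 | 0.83 |
| 15 | 0.48 | 0.79 |

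**3. What observing the outcome gains.** Power = Φ{[0.148·√n − 1.645·√(2p̄(1 − p̄))]/√(p₁(1 − p₁) + p₂(1 − p₂))}. With n = 60 it is 0.801; with n = 75 it is 0.874. The second is a ceiling, because unstimulated tACS patients dilute the effect. If 4 of 75 are unstimulated and have the sham rate (an assumption), the tACS rate is (71·4.9 + 4·19.7)/75 = 5.7% and power is 0.83. With 8 of 75 it is (67·4.9 + 8·19.7)/75 = 6.5% and 0.78. The power gain is therefore modest and can vanish.

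**4. Bias between arms.** Assume no true effect, POD risk q = 19.7% in both arms, a fraction d leaving, and leavers at r = 2 times the average risk. Stayers then show (q − d·r·q)/(1 − d). None of these d and r values is in the documents.

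| Leaving, tACS vs sham | Stayers, tACS vs sham | Apparent OR | One-sided rejection |
|---|---|---|---|
| 20% vs 20% | 14.8% vs 14.8% | 1.00 | 5% |
| 22% vs 18% | 14.1% vs 15.4% | 0.91 | about 7% |
| 25% vs 15% | 13.1% vs 16.2% | 0.78 | about 12% |

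Bias depends on unequal loss and disappears when loss is equal.

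**The case against.** The strongest reply is that section {11b} permits exit and does not require it: the verb is may, and no sentence says that visits stop. That stands. The end of screening is an inference from leaving the study. Continued visits might also be set out in a fuller protocol that is not shown. Even so, the article states a rule whose only patient-level consequence is leaving the study, and that rule points away from the stated analysis. This is more than an omitted detail.

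A reader might go further and infer that the rule removes the patients most at risk of delirium and leaves the analysis with no outcome for them. The documents do not support either step. The criterion also covers a contraindication found late, which has no stated link to POD. Section {20c} does plan an outcome for dropouts, though an imputed one.

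A reader might also infer that the loss favours tACS. Events before stimulation should not differ by arm under blinding. Only stops during the session could, since active current runs 20 minutes and sham 30 seconds. Section {22} describes side effects as mild and mostly no different from sham, and {11c} expects high adherence. Stopping for discomfort, or refusing a single visit, is not clearly covered by the criterion.

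Significance flips can also be produced by selecting counts. With 5 of 15 unseen patients positive in both arms, 17/75 vs 8/75 gives p = 0.024; with 3 of 15 in both, 15/75 vs 6/75 gives p = 0.017.

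Nor can it be said that the outcome is beyond recovery. Section {11d} states that enrolled patients in the covered departments "will not be visited or accompanied by the delirium prevention unit", but someone who has left the trial might come back under that unit's daily screening. The text does not settle this.

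**Conclusion.** The point holds as a conflict between two stated rules: {11b} merges ending the intervention with leaving the study, while {20a} needs follow-up whatever treatment was received. It should be fixed, but the documents do not show that it invalidates the trial.

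The main cost is lost precision and reliance on imputation with an unfixed direction: one-sided p of 0.007 or 0.054 from the same observed data at the upper bound of 15 missing per arm, and power of about 0.80 with 60 observed against at most 0.87 with 75. Since dilution can use up that gain, the firmer reason for the change is that the intention-to-treat effect would be observed and not imputed. Bias between arms is possible only if mid-session stops differ by arm, and the documents give no figure for that. The conclusion assumes that allocation takes place at enrolment, as {16b} indicates, and that leaving the study ends the visits.

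**What to change.** Split the patient-level part of {11b} into two categories.

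- **(a) Stimulation not given or stopped.** The patient stays in the study, visits V4–V13 (3D-CAM, RASS, NRS) continue on schedule where the patient can be assessed, and the reason and minutes of current delivered are recorded.
- **(b) Withdrawal of consent to follow-up.** Leaving the study is reserved for this category.

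For the outcomes that remain missing, fix before unblinding which single imputation applies to which known reason.

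This changes data collection only and leaves the criteria for giving or stopping stimulation untouched. It costs one protocol paragraph, a case report form line, a few more in-hospital visits and a slight dilution of the observed effect when few patients are unstimulated. Recruitment had begun, with 28 patients completed by April 2024, so an early amendment keeps more outcomes.

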### Strategies to improve adherence to interventions {11c}

The study involves a single-session transcranial electrical stimulation (tES) intervention in the post-anesthesia care unit (PACU), administered and supervised by study staff immediately after surgery. This controlled setting minimizes the chances of non-adherence, as patients are continuously monitored. The brief duration of the intervention (20 min) allows seamless integration with standard PACU procedures, further reducing the risk of protocol deviations. Together, these factors ensure a high level of adherence without the need for additional compliance strategies.

### Relevant concomitant care permitted or prohibited during the trial {11d}

Apart from the intervention and the close monitoring for POD during the postoperative visits, the participation in the study will not further affect the care of patients. Concerning the perioperative care, the anesthetic management protocols will not be modified by the trial. Induction and maintenance of anesthesia will be conducted according to the standard operating procedure of the clinic. The treating anesthesiologist will have access to the routinely used neuromonitoring devices and the indices of depth of anesthesia. If patients develop a POD, the treatment of productive delirious symptoms with antipsychotic drugs will be administered as prescribed by the treating ward physician.

At the Greifswald University Hospital, a delirium prevention unit has been implemented in the routine care of hospitalized patients of four departments (general surgery, orthopedy, internal medicine, and neurology). All patients over 65 years of age are screened daily by the unit, and non-pharmacological delirium prevention interventions are undertaken. Patients who are enrolled in the trial and admitted to one of these departments will not be visited or accompanied by the delirium prevention unit.

### Provisions for post-trial care {30}

N/a. No provisions for ancillary and post-trial care are expected to be relevant to this study.

### Outcomes {12}

#### Primary outcome measure

Incidence of POD as defined by having at least one positive 3D-CAM within the 10 visits in the 5 postoperative in-hospital days.

#### Secondary outcome measures

Duration of POD (days between first positive 3D-CAM score and last positive 3D-CAM score)Maximal POD severity (3D-CAM-S)Median and interquartile range of POD severity (3D-CAM-S)Delirium phenotype (RASS)Adverse eventsIncidence of emergency delirium in the PACU (PACU-D) as defined by having at least one positive 3D-CAM score in the PACUPostoperative pain in the PACU (NRS)Postoperative pain in the five first postoperative days (NRS)Presence of postoperative nausea and vomiting (PONV)EEG biomarkers from postoperative 64-channel EEG recordings including but not limited to total power, power within frequency bands, measures of periodic activity (power, center frequency, bandwidth), measures of aperiodic activity (offset, exponent), phase-lag-index, entropy measures, and burst-suppression-ratioPostoperative blood biomarkers

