### Intervention description {11a}

Patients will be enrolled at least 1 day before surgery. Questionnaires regarding contraindications for tES as well as baseline questionnaires will be handed out (PPI, HADS, STAI, PCS, BRI, PSQ, DN4). The preoperative cognitive status will be assessed with a MoCA score.

On the day of the surgery, a 64-channel EEG will be recorded in the preoperative holding area. Preoperative delirium and pain will be assessed with standardized tests (RASS, 3D-CAM, and NRS). A preoperative blood sample will be drawn. Before induction of anesthesia, a frontal EEG recording will be started that will last until the end of anesthesia.

A single tES intervention will take place postoperatively in the PACU, after return of consciousness and patient handover to the PACU staff. Emergence of delirium in the PACU (PACU-D) will be assessed, and patients will be asked about postoperative nausea and vomiting (PONV) as well as pain using standardized tests (RASS, 3D-CAM, and NRS) every 30 min for 1 h in the post-anesthesia care unit (PACU). A 64-channel EEG will be recorded, and a second blood sample will be drawn after the tES intervention.

During the first 5 postoperative days, patients will be screened twice daily for POD and pain using standardized tests (RASS, 3D-CAM, and NRS). A third blood sample will be drawn on the second postoperative day (Fig. 1).

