#### Postoperative visits

The RASS, the 3D-CAM, and the NRS score will be assessed once preoperatively in the holding area, every 30 min for 1 h in the PACU (3 times in total) as well as twice a day for 5 days postoperatively.

The Richmond Agitation-Sedation Scale (RASS) score is a commonly used tool to assess a patient’s level of agitation or sedation, ranging from + 4 (combative) to − 5 (unarousable), with 0 representing an alert and calm state [39]. Patients with a postoperative RASS score in the PACU of − 2 or below will not be questioned regarding POD or pain.

The 3D-CAM is a reliable, validated diagnostic assessment tool for delirium, based on a structured 3-min interview to identify the presence of POD and was translated and validated for the use in German [40, 41]. Based on the principle of the CAM method, “(…) the algorithm is considered positive if following features are present: Feature 1) Acute onset or fluctuating course and Feature 2) Inattention and either Feature 3) Disorganized thinking or Feature 4) Altered level of consciousness.”

If a patient is identified as delirious based on the 3D-CAM, the RASS score will be used to determine the phenotype of the delirium at the timepoint of the visit: hypoactive (RASS − 5 to − 1) or hyperactive (RASS + 1 to + 4).

Furthermore, the 3D-CAM-S score will be calculated from the 3D-CAM assessment. The 3D-CAM-S is a validated method derived from the 3D-CAM diagnostic interview for assessing delirium severity, demonstrating excellent agreement with the commonly used delirium severity scale, CAM-S Short Form, and is designed to provide prognostic information, monitor delirium progression, and evaluate treatment response in older patients undergoing major elective non-cardiac surgery [42].

The Numeric Rating Scale (NRS) is a self-report measure of pain intensity on a scale of 0 (no pain) to 10 (worst possible pain), used for assessing a patient’s self-reported pain level.

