#### Secondary outcome analysis

Binary logistic regression will be employed to adjust for baseline delirium status and to test differences between treatment (tDCS) and control (sham) in incidence of POD. Dependent variable will be incidence of POD (yes/no); independent variables are group (tDCS/sham) and baseline delirium status as measured by the 3D-CAM score. Odds ratio and corresponding 95% CI will be reported.Continuous variables (e.g., duration of delirium, severity scores, EEG biomarkers, fluid biomarkers) will be analyzed using analysis of covariance (ANCOVA) including the particular baseline value.Categorical variables (e.g., delirium phenotype) will be analyzed using binary logistic regression, adjusting for baseline 3D-CAM.For EEG and biofluid biomarker outcomes, linear mixed-models (LMM) will be implemented to account for within-subject correlations across time points.

In addition to the primary and secondary outcomes, exploratory analyses will be conducted on the collected blood samples to gain further insights into the biological mechanisms associated with postoperative delirium (POD) and the effects of transcranial electrical stimulation (tES). These analyses will focus on identifying associations between levels of various blood biomarkers—particularly markers of neuroinflammation, neurodegeneration, and other relevant pathways—and the incidence and severity of POD. Additionally, we aim to explore potential biomarkers that may be associated with differential responses to the tES intervention.

To better understand how patient characteristics influence treatment response, we will conduct subgroup analyses using blood biomarker profiles. These profiles, identified through exploratory cluster analysis, will help us group patients into distinct subgroups with potentially unique responses to tES. This approach could uncover specific biomarker patterns linked to differential treatment effects, paving the way for personalized POD prevention strategies. Recognizing the heterogeneity of our study population is crucial for interpreting our findings and guiding future research towards biomarker-driven, individualized treatments [45]. Our discussion will highlight the importance of considering patient diversity in POD risk and treatment response.

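### Delirium duration, taken as last minus first positive screen, gives 0 days to a single-screen case, and its ANCOVA calls for a baseline value that does not exist

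*Protocol article*

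**What the plan says.** Five statements in the protocol article bear on this outcome.

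- Primary outcome measure: a patient has POD with "at least one positive 3D-CAM within the 10 visits in the 5 postoperative in-hospital days". One positive screen is sufficient.
- Secondary outcome measures, first item: "Duration of POD (days between first positive 3D-CAM score and last positive 3D-CAM score".
- Secondary outcome analysis: "Continuous variables (e.g., duration of delirium, severity scores, EEG biomarkers, fluid biomarkers) will be analyzed using analysis of covariance (ANCOVA) including the particular baseline value". Duration is the first example in that list.
- Secondary outcome analysis, for categorical outcomes: "Categorical variables (e.g., delirium phenotype) will be analyzed using binary logistic regression, adjusting for baseline 3D-CAM". Here the covariate is named.
- Statistical methods {20a}: the analysis follows intention to treat, "including all randomized patients in the groups to which they were assigned, regardless of the treatment received".

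On what is measured before surgery, Intervention description {11a} says: "Preoperative delirium and pain will be assessed with standardized tests (RASS, 3D-CAM, and NRS". Postoperative visits and Table 1 agree that this is a single preoperative assessment.

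**The concern.** Two rules in the text misfire when followed as written.

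The first is the counting rule. When the first and last positive screens are the same screen, the interval between them is zero. The primary outcome counts that patient as delirious while the duration outcome records no time in delirium. The rule also ignores negative screens between two positive ones, and the Background section itself describes delirium as fluctuating.

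The second is the covariate. The ANCOVA sentence asks for each outcome's own baseline value. That works for EEG and blood markers, and plausibly for 3D-CAM-S severity. It does not work for duration, which has no preoperative counterpart.

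At stake is whether the first-listed secondary outcome means what its name says, and whether its analysis is settled before unblinding. Otherwise the analyst must choose among readings that can give different answers.

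**Working it through.** **Inputs.** The screening schedule is two visits a day on D1 to D5, 10 in all (Primary outcome measure; Table 1). The planning rates are 19.7% POD with sham and 4.9% with active treatment, with 60 per group before dropout and 225 in total (Sample size {14}). Allocation is 1:1:1, so 225 / 3 = 75 are randomised per arm.

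**The plan's own figures.** The article states no figure for duration. The planning figures used below do reproduce:

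- The odds ratio is (0.197/0.803) / (0.049/0.951) = 4.761.
- A one-sided 5% test with 80% power and no continuity correction needs 60 per group.
- 180 / (1 − 0.20) = 225.

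**Step 1: apply the duration rule to example courses.** The rule as written is the day of the last positive minus the day of the first positive.

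| Positive screens | As written (days) | Inclusive span (last − first + 1) | Days with a positive screen |
|---|---|---|---|
| None | not defined | not defined | 0 |
| D2 morning only | 0 | 1 | 1 |
| D2 morning and afternoon | 0 by date, 0.5 by visit | 1 | 1 |
| D2 morning to D3 morning, all positive | 1 | 2 | 2 |
| D1 morning and D5 morning only | 4 | 5 | 2 |

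The second row is a POD case with zero duration. In the last row the other eight screens are negative, and the rule gives twice the number of positive days. Against a count of positive days, then, the rule understates some courses and overstates others.

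**Step 2: look for a qualifying rule.** The article gives no added day, no minimum, no half-day unit and no value for patients who are never positive.

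**Step 3: look for a baseline duration.** The only preoperative delirium measurement is one RASS and 3D-CAM assessment. It yields a status and a derivable 3D-CAM-S score, but no duration. The baseline term in the ANCOVA cannot be formed for this outcome.

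**Step 4: share of patients without POD at the planning rates.**

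- Sham: 1 − 0.197 = 80.3%. Expected cases are 60 × 0.197 = 11.8, or 75 × 0.197 = 14.8.
- Active: 1 − 0.049 = 95.1%. Expected cases are 60 × 0.049 = 2.9, or 75 × 0.049 = 3.7.

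If all randomised patients are analysed and non-cases are set to 0, at least about 80% and 95% of the values are zero. Single-screen cases add to these under the rule as written.

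**The case against.** The strongest reply is that this is loose wording in a condensed article. A first-to-last span is a legitimate outcome in itself, and an inclusive count may be intended. The article does not say that duration is in whole days, so two positives on one day could count as 0.5. The ANCOVA sentence is generic, and for duration its baseline could mean the preoperative 3D-CAM. The value given to non-cases is ordinary analysis-plan content, and that plan is not at hand.

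Much of this stands. The same-day case depends on the unit. The confusion with non-cases arises only if they are coded 0, which the article does not state. ANCOVA on data with many zeros is not necessarily invalid at this sample size. What does not go away is the single-screen case, which is 0 in any unit, and the naming of duration for a model with its own baseline. Two lines on, the same section names baseline 3D-CAM for the categorical outcomes, so the different wording for duration cannot simply be read as that covariate.

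Three stronger readings are tempting and are not supported.

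- *Duration is understated for every delirious patient.* This holds only against an inclusive span. The D1 and D5 course shows overstatement against positive days.
- *The between-arm difference is halved.* With an assumed mean of 2 inclusive days, (0.197 − 0.049) × 2 = 0.30 day becomes 0.148 × 1 = 0.15 day. Assumed means of 1.5 and 3 days give 0.22 to 0.07 and 0.44 to 0.30. The article gives no episode length. The sum also needs the same mean in both arms and zero coding of non-cases, and it compares with a span and not with the count proposed here. Among delirious patients alone, subtracting one day from everyone leaves the difference unchanged.
- *The comparison will be restricted to delirious patients, and so selected after randomisation.* Nothing says so, and the intention-to-treat statement points the other way.

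**Conclusion.** The point holds as a defect in two stated rules for one secondary outcome. A patient who meets the POD definition on a single screen is given 0 days, and a course with gaps can be given more days than were positive. The ANCOVA names a baseline value that is never measured. These conclusions follow from the text and need no assumption.

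That single-screen cases become indistinguishable from patients without delirium is conditional on coding never-positive patients as 0. That most values are zero rests on the same coding, on analysing all randomised patients and on the planning rates. The amount by which the treatment effect on duration would be diluted cannot be fixed from the document.

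The point is worth correcting but is limited in weight. The primary outcome, its analysis and the sample size are untouched.

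**What to change.** Define duration as the number of postoperative days from D1 to D5 with at least one positive 3D-CAM, set to 0 for patients who are never positive, and analyse it in all randomised patients. Every POD case then scores at least 1, and negative days between positive ones are not counted.

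Take duration out of the sentence that calls for the outcome's own baseline value. Either use no baseline term for it, or adjust for preoperative 3D-CAM status as the logistic models do. Compare arms with a method suited to an ordinal count from 0 to 5 with many zeros, such as a rank-based or proportional-odds analysis.

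The cost is a small change to one secondary outcome definition and its analysis wording, made before unblinding. It uses 3D-CAM data already collected and needs no extra visit or patient.
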